**Frequency and methods of "visits":**

- From the 7th day after the booster vaccination, remote visits will be conducted at a frequency of twice a week (2-3 days' intervals is recommended), until the 90th day after vaccination: (1) If the number of confirmed primary endpoint cases reaches 162, the frequency of visits will be adjusted to once a month, until the 180th day after vaccination; (2) If the number of confirmed primary endpoint cases does not reach 162, remote visits will still be conducted twice a week. When the number reaches 162, the visit frequency will be adjusted to once a month, until the 180th day after vaccination;
- If the participant has a positive result of SARS-CoV-2 nucleic acid or antigen detection, no matter what stage he/she is in, he/she will be visited twice a week (2-3 days' interval is recommended), until his/her nucleic acid or antigen detection result turns negative or the symptoms disappear or stabilize under the investigator's assessment;
- Remote follow-up methods include text messages, phone calls, videos, photos, etc. On-site visits are carried out according to the above monitoring process and actual conditions.

---

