### **6.5. Sample size and groups**

#### **6.5.1. Sample size estimation**

This study is a randomized, blinded, placebo-controlled clinical study. The sample size for this study is estimated as follows:

Sample size of protective efficacy: Assume that the incidence rate of COVID-19 in the study area will be approximately 9% and the expected VE of the vaccine will be at least 60%. The superiority margin of VE is 30%, the allocation ratio of the experimental group to the placebo control group is 1:1, the test level is 0.025 on one side, and the power of the test is 90%. The sample size is calculated using the exact conditional method under the large-sample Poisson distribution based on Chan and Bohidar. At least 162 confirmed cases of COVID-19 with clinical symptoms should be collected in the study, and a sample size of 1,286 participants is required for each

---

group. Considering about 20% non-evaluable rate, 1,600 participants are planned to be enrolled in each group, with a total of 3,200 participants.

Due to the unpredictability of the number of cases in some areas and the change in the incidence rate in different regions, the number of COVID-19 cases will be monitored blindly during the research. The number of participants planned to be enrolled can be increased during the study according to the changes of the incidence in different regions, but the required number of clinically symptomatic COVID-19 cases of any severity cannot be changed, thus not causing inflation of the overall Type I error of the study.

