## 6.6. Observation of protective efficacy

**7 days after the booster vaccination for every participant, the investigators need to carry out the following "routine monitoring" on the participants through a combination of remote visits and on-site visits:**

- The investigators remotely visit the participants to see if they have symptoms related to COVID-19;
- When the investigator learns that the participant has any one or more of the following conditions through remote visits, it is necessary to collect the participant's throat swab sample A1 (for SARS-CoV-2 nucleic acid or antigen detection), and further inquiry, record, and guidance should be done to the participant to continue to observe and record symptom types, start and end time, severity, etc. If an on-site visit is conducted to the participant (the on-site visit could be carried out by the participant going to the study site or the investigators' visit), another nucleic acid throat swab sample B1 (backup sample) needs to be collected:

④ *Any possible signs or symptoms related to COVID-19 appear (fever or chills, malaise/fatigue, headache, dry throat, muscle pain, sore throat, nasal congestion/runny nose, anorexia/nausea/vomiting, diarrhea, new sense of smell/dysgeusia, conjunctivitis);*

⑤ *Any one or more respiratory-related symptoms (cough, shortness of breath, or dyspnea) appear and last for any time;*

⑥ *Clinical or imaging evidence of pneumonia.*

**If the result of SARS-CoV-2 nucleic acid or antigen detection of the participant's throat swab sample A1 is positive, the investigators need to**

---

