## **6.9. Follow-up plan**

Within 28 days after the booster vaccination, all participants need to conduct at least 3 on-site visits to complete enrollment (visit 1), vaccination (visit 1), distribution, and collection of diary cards and contact cards (visit 1, visit 3, visit 4). The participants in the immunogenicity subgroup also need to collect blood for immunogenicity (visit 1-6).

From the 7th day to the 180th day after the booster vaccination, all participants

---

need to conduct remote visits at least 22 times (about 8 times per month from the 7th day to the 90th day after the vaccination; about once per month from the 90th day to the 180th day after the vaccination), to carry out routine monitoring of VE and/or case monitoring after booster vaccination. At the same time, AEs, SAEs, AESIs, and pregnancy events (including pregnancy outcomes, delivery characteristics, the condition of the newborn, and the growth and development within 1 month after birth) need to be collected.

In addition to the on-site visits and remote visits mentioned above, the investigators may increase the on-site visits or remote visits to the participants to an appropriate frequency according to actual needs, and make follow-up records.

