#### **11.8.2.3. Protection effectiveness analysis**

The person-year incidence rates and 95% confidence interval(CI) of COVID-19 confirmed by the central laboratory with clinical symptoms will be calculated among the test group and the control group 14 days after the vaccination, and the Poisson regression model will be used to analyze the statistical differences between the groups. VE and 95% CI based on the person-year incidence rates will be estimated with the model. The Poisson regression model takes the number of patients as the dependent variable, grouping as the fixed effect, and the exposure person-years of the participants as the offset, using the log connection function.

Person-year incidence rate=(number of cases)/(exposure person-years of the participants)×100%. In the calculation of the exposure person-years, the starting time is the 14th day after the vaccination, and the ending time is the day when a COVID-19 case was first confirmed. If the RT-PCR or antigen test was positive but not confirmed as a COVID-19 case, the person-year incidence rate was calculated using the RT-PCR or antigen test date as the termination time. VE rate=1- (person-year incidence rate of the test group)/(person-year incidence rate of the control group).

---

The VE will be evaluated in the prevention of clinically symptomatic COVID-19 confirmed by central laboratory virology 14 days after vaccination based on the sets of E-mFAS and E-PPS. The evaluation of VE based on E-mFAS is the main analysis result of this study.

In addition, the VE of the vaccine against clinically symptomatic COVID-19 confirmed by central laboratory virology 7 days after vaccination will be evaluated based on E-mFAS, and the statistical method is the same as the primary efficacy endpoint.

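### Sections 6.6 and 6.9 disagree on case-finding after day 90, and the person-time rule does not stop when contact thins to monthly

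*Protocol*

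**What the plan says.** **Contact frequency, Section 6.6** (repeated in 11.3.2 and in the synopsis under observation of protective efficacy). Remote contact is twice weekly from day 7 to day 90 for everyone. After day 90 it becomes monthly if 162 primary-endpoint cases have been confirmed. If not, it stays twice weekly: "When the number reaches 162, the visit frequency will be adjusted to once a month, until the 180th day after vaccination".

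**Contact frequency, Section 6.9** (repeated in the synopsis follow-up plan). About eight contacts a month are planned from day 7 to day 90, then "about once per month from the 90th day to the 180th day after the vaccination". The 162-case condition is absent.

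**How a case is found.** Under 6.6 the swab follows "When the investigator learns that the participant has any one or more of the following conditions through remote visits". Appendix 1 requires a positive nucleic acid or antigen test in addition to symptoms or evidence of pneumonia.

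**Person-time.** Section 11.8.2.3 starts the clock on day 14, and "the ending time is the day when a COVID-19 case was first confirmed". A positive test that is not confirmed as a case also ends it. The rule names no stop at the change of contact frequency, at the 162nd case or at a data cut. Section 6.5.1 asks for at least 162 cases, and 11.2.7 runs efficacy visits to day 180.

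**The concern.** Two parts of the same protocol give the site different surveillance intensities for the primary endpoint over days 90 to 180. They differ exactly when it matters, when the trial is short of cases. Since contact is the stated trigger for the swab, contacting participants monthly instead of twice weekly means that illnesses which begin and clear between calls may never be tested. The immediate stake is the case target and the power attached to it.

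The second stake is the estimate. Once contact is monthly, the chance of finding an illness rises with its length. If person-time under both intensities is pooled, and if vaccinated participants have shorter detectable illness, fewer of their cases are found per true case and VE comes out too high.

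**Working it through.** **1. The plan's own figures.** Section 6.5.1 gives VE 60% (rate ratio 0.40), margin 30% (rate ratio 0.70), 1:1 allocation, 90% power, control incidence 9%, and "the test level is 0.025 on one side".

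- In the exact conditional test, the vaccine-arm share of cases is 0.7/1.7 = 0.4118 at the margin and 0.4/1.4 = 0.2857 under the alternative.
- The smallest total from which power stays at or above 90% is 160. At 162 the critical value is 54 vaccine-arm cases, exact one-sided alpha is 0.0247 and power is 92.2%.
- Participants per arm: 162/(0.09 × 1.4) = 1,285.7, so 1,286 as stated.

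The 162 cases are therefore sound, provided they are found.

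**2. Where the two schedules part.**

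| Situation at day 90 | Section 6.6 | Section 6.9 |
|---|---|---|
| 162 cases reached | monthly | about monthly |
| 162 cases not reached | twice weekly until reached | about monthly |

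Only the second row conflicts. Days 90 to 180 are 90 of the 166 days from 14 to 180, or 54% of maximum person-time.

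**3. Cases and power if 6.9 is followed with cases short.** The documents give no illness durations, so the detectable window w is an assumption. Detection is min(1, w/3.5) under twice-weekly contact and min(1, w/30) under monthly contact, with no self-reporting. Suppose 162 cases would occur evenly over days 14 to 180. Then 162 × 76/166 = 74.2 fall before day 90 and 87.8 after it.

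| Window (days) | Detected monthly | Cases found | Power at VE 60% |
|---|---|---|---|
| 7 | 23% | 74.2 + 20.5 = 95 | 71% |
| 10 | 33% | 74.2 + 29.3 = 103 | 75% |
| 14 | 47% | 74.2 + 41.0 = 115 | 78% |

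No difference between arms is needed for this loss.

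**4. Effect on the pooled VE.** Assume monthly contact for everyone from day 90 and a constant hazard. In day-equivalents, the placebo arm contributes 76 + 90 × w_P/30 and the vaccine arm (1 − VE) × (76 + 90 × w_V/30).

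- Equal windows: the brackets cancel, and 60% stays 60%.
- Placebo 10 days, vaccine 8: 1 − 0.4 × 100/106 = 62%.
- Placebo 10, vaccine 7: 1 − 0.4 × 97/106 = 63%.
- Placebo 10, vaccine 5: 1 − 0.4 × 91/106 = 66%.

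A true 30% becomes 34%, 36% or 40% with the same windows.

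**5. Effect on the one-sided error if 6.6 is followed.** Take true VE 30%, 162 fully ascertained cases, then 100 further true cases under monthly contact, all pooled. With windows 10 and 8 days:

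- Placebo: 95.3 + 58.8 × 10/30 = 114.9.
- Vaccine: 66.7 + 41.2 × 8/30 = 77.7.
- Apparent VE: 1 − 77.7/114.9 = 32%.

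The design's exact test then rejects with probability 0.034. With vaccine windows of 7 and 5 days the figures are 0.041 and 0.069, against 0.0215 with equal windows.

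**The case against.** Much can be said for the plan.

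- **The step-down in 6.6 is guarded.** It needs both day 90 and 162 cases. A reader might infer that surveillance thins for everyone at the 162nd case; the text does not say that.
- **6.6 looks like the governing text.** Section 11.2.7 sends efficacy surveillance to 6.6, 11.3.2 repeats the case condition, and the trial has a single centre. Section 6.9 speaks of minimum and approximate numbers and lets investigators add contacts. This makes an actual loss of cases less likely, but two schedules still stand in the document the site works from.
- **Pooling is not stated.** Section 6.11.5 allows database lock once the primary objectives are achieved, which could mean near case 162. The person-time rule also gives no end for participants who never become cases, so it is incomplete rather than a decision to pool. A data cut may be in the SAP, which is not at hand. This objection stands as far as it goes: the protocol permits pooling without prescribing it.
- **Self-report exists.** Section 4.2.2 foresees participants reporting suspected or confirmed cases. Any such reporting shrinks every figure above.
- **Thin contact is not bias in itself.** In a blinded trial with equal detectable windows the rate ratio is unaffected.

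A reader might also take the 22 remote visits in 6.9 for an error, since its frequencies give 8 × 83/30 = 22.1 up to day 90 and about three more after it, roughly 25. The number is stated as a minimum, which 25 satisfies, and the schedule footnote drops telephone visits that coincide with on-site ones. It is not an error.

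**Conclusion.** The contradiction between 6.6/11.3.2 and 6.9 with the synopsis is real, and a SAP cannot settle it because it concerns what the site does. It takes effect only if 162 cases have not been confirmed by day 90. Then, under assumed 7-to-14-day windows, even accrual and no self-reporting, following 6.9 would yield about 95 to 115 cases and about 71 to 78% power, against the stated 90%.

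The person-time point is a conditional risk. A reader might infer that the primary VE is already biased. The documents do not support this: they give no illness durations, and they leave open whether post-step-down data enter. If those data enter and vaccine-arm illness is shorter, the assumed fixed windows move a true 60% to about 62 to 66% over the whole period. A larger figure is easy to produce for the monthly period alone (with windows of 7 and 5 days, 1 − 0.4 × 5/7 = 71%), but that is not the primary estimate.

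**What to change.** 1. Reword 6.9 and the synopsis follow-up plan to match 6.6: monthly contact applies to a participant only after both day 90 and the 162nd confirmed case.
2. In 11.8.2.3, for the primary analysis, count each participant's cases and person-time only up to the date that participant moves to monthly contact. Present later data as supplementary.

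The stop should be set per participant. A calendar cut at the 162nd case would discard twice-weekly, fully ascertained data from participants not yet at day 90. If 162 cases are never reached, 6.6 keeps contact twice weekly and no such censoring occurs.

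The cost is wording in two sections and the synopsis, with no visits beyond those 6.6 already requires. The downside is that cases found after the step-down no longer count in the primary estimate. The design figures are kept: by the time anyone is censored, 162 cases have been found under twice-weekly contact, which gives 92.2% power and an exact alpha of 0.0247.

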## **6.7. Safety observations**

All participants need to be followed up for safety:

### **➤ Safety observation from 0 to 28 days after booster vaccination**

All participants will collect all adverse events occurring within 30 minutes after vaccination, solicited inoculation site (local) and non-inoculation site (systemic) adverse events within 0-14 days, and unsolicited adverse events within 0 to 28 days.

### **➤ Long-term safety observation**

All serious adverse events (SAEs), adverse events of special interest (AESIs), and pregnancy-related events within 6 months after vaccination will be collected from all participants.

## **6.8. Immunogenicity observation (for immunogenicity subgroup only)**

For participants in the immunogenicity subgroup (100 cases), venous blood samples of approximately 15 mL will be collected before booster vaccination, 7 days, 14 days, 28 days, 3 months, and 6 months after booster (a total of 6 times). Separated serum will be detected for the virus-neutralizing antibody against the current main epidemic strain and specific S-protein IgG antibody.

Extra venous blood samples of the participants in the immunogenicity subgroup (100 cases) will be collected before vaccination, 7 days, 14 days, 28 days, and 3 months after booster (5 times in total) to detect cytokines of IL-2, IL-4, IL-13, and IFN- $\gamma$  (ELISpot).

## **6.9. Follow-up plan**

Within 28 days after the booster vaccination, all participants need to conduct at least 3 on-site visits to complete enrollment (visit 1), vaccination (visit 1), distribution, and collection of diary cards and contact cards (visit 1, visit 3, visit 4). The participants in the immunogenicity subgroup also need to collect blood for immunogenicity (visit 1-6).

From the 7th day to the 180th day after the booster vaccination, all participants

---

need to conduct remote visits at least 22 times (about 8 times per month from the 7th day to the 90th day after the vaccination; about once per month from the 90th day to the 180th day after the vaccination), to carry out routine monitoring of VE and/or case monitoring after booster vaccination. At the same time, AEs, SAEs, AESIs, and pregnancy events (including pregnancy outcomes, delivery characteristics, the condition of the newborn, and the growth and development within 1 month after birth) need to be collected.

In addition to the on-site visits and remote visits mentioned above, the investigators may increase the on-site visits or remote visits to the participants to an appropriate frequency according to actual needs, and make follow-up records.

## **6.10. Data collection**

The necessary data for statistical analysis will be collected using an electronic data capture (EDC) system.

## **6.11. Randomization and Blinding**

### **6.11.1. Randomization**

The randomization statistician will use SAS statistical software and generate randomization blind code with the method of "block randomization". After the investigator confirms that the participant is eligible for inclusion and signs the informed consent, the participant will be assigned a randomized study number (randomization number). The investigator will choose the investigational vaccine or placebo with the same number as the randomization number and give the injection to the participant. For the randomized participants who withdraw from the clinical study for any reason, regardless of whether they have been vaccinated with the investigational vaccines before, their randomization numbers will be retained and not be distributed again, and the participants will not be permitted to participate in this study.

Back-up vaccines: The block randomization method will be used to generate a randomization list of back-up vaccines, with a total of 320 vaccines (160 study

---

vaccines and 160 placebos). When the backup vaccine is used, the investigator should log into the back-up vaccine system to obtain the corresponding number of the back-up vaccine.

### **6.11.2. Blinding**

An observer-blinded design will be used for this study. Before the study, the randomization statistician will provide the randomization table to the unblinded investigators who are authorized to perform vaccination-related work, and the unblinded investigators will give the injections according to the groups corresponding to the randomization numbers in the randomization table. Because the LVRNA021 vaccine and placebo are different in physical appearance, the investigators should set up blinding measures, including but not limited to syringes shading, room partitions, eye masks, etc., to prevent the participants from identifying the type of investigational vaccines based on their appearances.

The duties of drug dispensing and administration in the unblinded team must be assigned to one or more investigators who are not involved in any study of participants' evaluation. Unblinded teams and managers should avoid touching the participants as much as possible. Blind must be maintained during the generation of randomization numbers and the preparation of blind codes, the random allocation of vaccines, the vaccination of the participants, the results recording and efficacy evaluations of the investigators, the monitoring of the monitors, and data management.

Due to the inherent difference in liquid color between the study vaccine and the placebo, to ensure the feasibility of blinded design, it is necessary to appoint unblinded study staff outside the investigator's observation team for vaccination, and they are required not to disclose the participant grouping information to other relevant staff involved in the trial. To ensure that the participants are blinded, during the trial, the risk of the subjects guessing the group from the appearance of the investigational vaccine should be avoided, which may cause bias in the evaluation of safety or efficacy. Investigators who have been authorized to perform vaccination shall not be authorized to engage in tasks that may lead to unblinding such as subject blood

---

sample collection, efficacy follow-up, or safety follow-up, to ensure the blind maintenance during subject follow-up and immunogenicity blood sampling. For other specific operation instructions, please refer to the Pharmacy Manual.

#### **6.11.3. Vaccine blinding**

The vaccines used in this study will not be blinded.

#### **6.11.4. Emergency unblinding**

Only in emergencies or when serious adverse events occur, and the information of the investigational product is critical to the clinical treatment or health of the participants, it is necessary to conduct individual emergency unblinding and make relevant records, after the confirmation by the principal investigator and sponsor. The participant with this study number will terminate the study as a dropout, and the investigator will record the reason for termination in the "Vaccination and Follow-up Record Book".

If group adverse events occur or the study needs to be interrupted for any reason, the unblinding could be done in advance with the approval of the sponsor.

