#### **4.4. Benefit/risk assessment**

Because the preventive effect of the study vaccine against disease caused by SARS-CoV-2 infection, same as any other study vaccine, may not be 100%. Because it is possible that subjects may enter the placebo group and may not develop protection against SARS-CoV-2 infection after vaccination, there remains a risk of morbidity from natural infection with SARS-CoV-2.

Based on the following considerations, participation in this study subjects exposed to a low risk of developing unknown adverse reactions.

- 1) According to the animal toxicity test of this product suggests that the safety risks associated with it can be minimized during clinical studies by following the vaccination dose and vaccination protocol specified in the study protocol and by close monitoring.
- 2) The clinical study protocol establishes strict criteria for termination/suspension of the study.
- 3) During the study, the investigator will focus on the safety evaluation and the solicited local adverse events, solicited systemic adverse events, and other adverse events after vaccination. Risk control measures, including appropriate enrollment and exclusion criteria, close monitoring of subjects, and suspension/early termination criteria, will be established before the study begins to ensure maximum benefit to the subjects.

---

Based on these safeguards, the potential risks associated with the study vaccine are reasonable concerning the benefits that could be realized for the prevention of COVID-19 in subjects.

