#### **6.12. Study suspension or termination criteria**

The sponsor reserves the right to suspend/terminate the study at any time. After full consultation with the sponsor and the sponsor's consent, the investigator could suspend or terminate the work of the research center. Reasons for suspending or terminating the study may be, but are not limited to, the following:

- (1) It is clear that the investigational vaccine lacks efficacy;
- (2) The incidence or severity of adverse reactions indicate that there may be potential dangers that may endanger the life of the participants;
- (3) The sponsor suspends or terminates the research voluntarily;
- (4) Suspend or terminate due to regulatory agency requirements.

During the study, if any of the criteria triggering the study suspension occurs, the safety of the investigational vaccine will be assessed by the investigator.

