#### 11.4.4. Relationship between adverse events and vaccine

Investigators should have measures to determine the causality of all AE and abnormal laboratory indicators to vaccination promptly, to identify SAEs and groups, convergent AE related to vaccination during clinical studies, and to suspend and terminate clinical studies on time to minimize harm to participants. Whether the adverse event is related to vaccination and the degree of correlation shall be determined according to the following principles.

**Not related:** the participant did not use the investigational vaccine, the AE occurred in an illogical chronological sequence with the administration of the investigational vaccine, or other significant causes could have led to the AE.

**Unlikely related:** evidence of investigational vaccination; AE more likely to be due to other causes; repeat investigational vaccination negative or inconclusive

**Possibly related:** evidence of investigational vaccination; temporal sequence of AE to investigational vaccination is reasonable; AE cannot be ruled out as being caused by

---

the investigational vaccine but may also be due to other causes.

**Probably related:** evidence of investigational vaccination; the chronology of AE with investigational vaccination is reasonable; AE is more plausibly explained by investigational vaccine than other causes.

**Related:** evidence of vaccination with the investigational vaccine; the temporal sequence of the AE with the administration of the investigational vaccine is reasonable; the AE is more plausibly explained by the investigational vaccine than by other causes; repeated positive vaccination with the investigational vaccine; the AE profile is consistent with previous knowledge of this or this type of vaccine.

Of these, "definitely related", "probably related", and "possibly related" were classified as "vaccine-related". "Unlikely related" and "Not related" are classified as "not vaccine-related"

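### Individual emergency unblinding must wait for sponsor confirmation, although site staff already hold the allocation and no emergency exception lets them release it

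*Protocol*

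**What the plan says.** Protocol 6.11.4 limits individual emergency unblinding to emergencies or serious adverse events in which "the information of the investigational product is critical to the clinical treatment or health of the participants". In those cases "it is necessary to conduct individual emergency unblinding and make relevant records, after the confirmation by the principal investigator and sponsor". The consequence for the person unblinded is also fixed: "The participant with this study number will terminate the study as a dropout".

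On who knows the allocation, 6.11.2 says that "the randomization statistician will provide the randomization table to the unblinded investigators who are authorized to perform vaccination-related work". Section 6.11.6 then has unblinded staff sign a confidentiality agreement and promise not to reveal allocation to others, naming the investigators among those others. It states no exception for emergencies. Section 6.11.2 gives the vaccinators a similar instruction.

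On suspending the site, 6.12 and the matching synopsis entry say: "After full consultation with the sponsor and the sponsor's consent, the investigator could suspend or terminate the work of the research center". One of the reasons then listed is "The incidence or severity of adverse reactions indicate that there may be potential dangers that may endanger the life of the participants". No separate rule is given for safety grounds.

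**The concern.** The unblinding rule applies only after someone has judged that product identity is critical to a participant's care. Waiting for a further party is hardest to justify at that moment. If the sponsor cannot be reached, the protocol as written leaves the clinician without the allocation, even though colleagues at the same site have it.

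What is at stake is the care of an individual participant, not inference. The point has no bearing on the sample size, the power or the one-sided 0.025 test level.

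The suspension wording raises a smaller question of the same kind. Section 4.4 gives as one of its reasons for rating participant risk as low that "The clinical study protocol establishes strict criteria for termination/suspension of the study". A reader should therefore be able to see from 6.12 that the site may pause at once for a safety signal.

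**Working it through.** No arithmetic applies, so the check sets the relevant sections side by side.

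**Unblinding**

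1. *Who must agree beforehand.* Under 6.11.4 both the principal investigator and the sponsor must confirm before the code is broken. No alternative order is written for urgent cases.
2. *When the rule applies.* Only when the information is critical to treatment or health. The usual remark that unblinding seldom changes acute care is therefore already built into the rule: cases where it would not matter are screened out before confirmation is sought.
3. *Where the allocation sits.* Under 6.11.2 the unblinded vaccination staff have the randomization table. The sponsor's confirmation is a permission, not a source of information.
4. *Whether the holders may release it.* Section 6.11.6 says they may not, and it names investigators among those who must not be told. With no exception there, the only written path is the one in 6.11.4. Changing 6.11.4 alone would leave the staff with the table still bound to silence.
5. *How long the wait could be.* Section 12.5.1 gives the investigator 24 hours to report an SAE. It gives the sponsor 7 calendar days for a fatal or life-threatening SUSAR, a further 8 for follow-up information, and 15 for other SUSARs and other serious safety-risk information. All of these concern onward reports. None limits the time the sponsor may take to confirm under 6.11.4. The wait could be one short telephone call or much longer; the protocol supports no figure, and none is claimed.
6. *What an unblinding costs.* The participant becomes a dropout under 6.11.4, but 7.4 keeps data collected before withdrawal available for analysis.

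**Suspension**

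7. The sponsor-consent sentence in 6.12 concerns suspending or terminating the work of the center. Danger to life is among the reasons listed, and no safety exception is written.
8. Section 11.4.4 mentions timely action: "and to suspend and terminate clinical studies on time to minimize harm to participants". In its sentence, what investigators must have is a means of judging causality promptly. Recognising SAEs and stopping in good time are what that judgement is for. The section names a purpose and does not create a separate power to suspend, so it does not conflict with 6.12.
9. The investigator already decides each enrolment (11.2.1 item 3; exclusion 14 in 7.2) and can end an individual's participation for safety or unsuitability (7.3, items 2 and 5). Each participant receives a single dose on Day 0 (9.3), so a hold protects only people not yet vaccinated.

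Steps 1 to 4 establish the unblinding point from the text. Steps 7 to 9 leave only a wording gap in 6.12.

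**The case against.** The strongest reply is that the rule rarely bites. There is one dose, and the comparator is saline (9.1). Care does not depend on the code: 12.2 provides an on-site emergency room, fast-track hospital admission and an SOP, and 12.4 requires an emergency plan for SAEs. The trial is to follow GCP and the Declaration of Helsinki (14.1), and operating detail is left to SOPs and a Pharmacy Manual that are not shown. A telephone call could count as confirmation. The gate also has a purpose, since every unblinding turns a participant into a dropout in a trial that needs 162 cases.

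Most of this stands as a limit on size. It does not answer the point. Treatment can start blinded, but 6.11.4 deals with cases where the product information itself is critical. General adherence to GCP does not rewrite an explicit sequence of approvals. Protecting the case count is a reason to keep unblinding rare, which the criticality condition and the principal investigator's confirmation already do.

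It is also fair to ask why only the sponsor's gate should go when the principal investigator's is a prior gate too. The principal investigator is appointed by the one research site (13.1) and a delegate can act in an absence. The sponsor's step adds an outside party to a decision about one person's care.

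A reader might go further and infer that the investigator is powerless to halt vaccination on a safety signal, or that 6.12 contradicts 11.4.4. The documents do not support either reading. Section 6.12 can be read as governing formal suspension of the center's work, nothing in it obliges the investigator to keep enrolling while the sponsor is consulted, and 11.4.4 states a purpose and not a rival authority.

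**Conclusion.** The point holds for 6.11.4. In an emergency where product identity is critical to care, the protocol makes unblinding wait for a party that is not needed to supply the allocation, and 6.11.6 closes the shorter route through site staff. This is a rule the protocol states, not detail left to a statistical analysis plan.

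Its size is modest. It concerns one site and 3,200 planned participants, 1,600 of them to receive the vaccine, with one dose each. How many would ever need unblinding, and how long confirmation would take, cannot be derived. It should not be inferred that emergency treatment itself would be delayed, because 12.2 and 12.4 provide for it regardless of allocation.

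The conclusion assumes that 6.11.4 and 6.11.6 are followed as written and that no unseen SOP supplies an exception. If one does, the protocol should say so.

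The wording of 6.12 merits a clarification only.

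**What to change.** 1. **6.11.4:** let the principal investigator or a named delegate authorise individual emergency unblinding immediately when it is needed for care. Replace prior sponsor confirmation with prompt notification afterwards, for example within the 24 hours already used in 12.5.1.
2. **6.11.6:** add a matching emergency exception so that unblinded staff may give that participant's allocation to the authorised clinician and to no one else. Cross-refer to it from the similar instruction in 6.11.2.
3. **6.12 and synopsis (secondary):** state that the sponsor-consent condition does not prevent the investigator from immediately pausing enrolment and vaccination on safety grounds, with prompt notice to the sponsor and the ethics committee. Sponsor consent can remain for termination and for suspension on other grounds.

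The study-level rule in the second paragraph of 6.11.4, on group events or interruption of the study, is a separate matter and is left as it is.

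The cost is wording in these sections, with no added staff, visits or data. The downside is an occasional unblinding that the sponsor would have declined. That participant becomes a dropout under 6.11.4, with data up to withdrawal still usable under 7.4. There may also be an occasional precautionary pause.
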